##### Knowledge of risk factors for development of depression and risk-reduction strategies

Environmental factors count for about 40% of developing major depressive disorder. (False)

Genetic factors count for about 80% of developing bipolar disorder. (True)

Having a family history of depression means that a person will definitely get depression. (False)

Chronic stress or having a disability or long-term health condition can increase one’s chances of developing depression. (True)

Being female and drug misuse both can decrease the chance of developing depression. (False)

Parental style does not appear to increase chance of developing depression in people with a family history of depression. (True)

Psychological therapies are very effective in preventing the development of depression. (True)

Regular exercise is definitely not effective in preventing the development of depression. (False)

Lifestyle behaviors such as getting enough sleep, eating a Mediterranean diet, and getting enough vitamin D are definitely not effective in preventing the development of depression. (False)

Having a positive attitude, good social support and greater spiritual well-being may be effective in preventing the development of depression. (True)

##### Intention to adopt, and actual adoption of, risk-reduction strategies

We would like to know whether you would make changes to your lifestyle to reduce your chance of developing depression. Please indicate from the list below how likely you would be to undertake these risk-reducing strategies. Have you...

…used psychological therapy to reduce your chance of developing depression?

…been exercising at a moderate-intensity for 30 minutes of each day to reduce your chance of developing depression?

…been getting adequate amounts of sleep (7-9 hours of sleep each day) to reduce your chance of developing depression?

…been eating a Mediterranean-style diet (rich in vegetables, fruits, nuts, whole grains and fish) to reduce your chance of developing depression?

…been getting the recommended daily intake of vitamin D (either from the spending time in the sun or through food and supplements) to reduce your chance of developing depression?

…been getting good social support to reduce your chance of developing depression?

…been maintaining a positive attitude towards most things to reduce your chance of developing depression?

…joined a religious group or developed your spirituality to reduce your chance of developing depression?

### Intervention

Following completion of the baseline questionnaire, intervention group participants will be directed to the intervention, which is entitled 'Understanding depression that runs in families’, and has three components: (i) feedback of family history assessment and screening test for depression symptoms; (ii) psycho-educational materials, which will be presented in the form of screens containing written information, illustrations and photos; (iii) short video clips, featuring two experts in depression and actors, which will supplement the information covered in the written text; and (iv) an interactive component where participants will be asked to rank the risk-reducing strategies they would like to implement. Upon entry, the results from the family history risk assessment and the screening test for depression (PHQ9) will be fed back to both the participant and, if the participant opts to share the results with their GP, to the GP, in the form of a one page report. Feedback to the GP will via e-mail or fax, according to the GP’s preference, for inclusion in the patient’s file; or the participant may opt to provide the GP with a paper copy of his/her results. The printable or viewable feedback will include details on the participant’s family history as ascertained by the Family History Screen and one of five depression screening feedback reports, with different recommendations depending on the participant’s depression severity category: do nothing, or recommendations regarding follow-up screening, treatment plan, initiation of treatment and/or referral to a mental health specialist [43]. The intervention was developed using an iterative process involving a multidisciplinary team, including one consumer representative. The development and pilot-testing of the intervention will be reported separately in detail. The content and format of the intervention was based on the information preferences expressed in a previous qualitative study of 23 people with a family history of MDD [[name]*, [name]*, [name], [name], [name], [name], [name]: Preferences regarding targeted education and risk assessment in people with a family history of major depressive disorder *joint first authors, submitted], where most participants reported being interested in accessing depression information via the internet. Also, while we recognize that a web-based tool excludes those without Internet access, it is the best means of reaching the largest numbers of individuals at a very low cost. It can also be readily updated as evidence accumulates in this rapidly developing field of genetics and depression.

The intervention meets the Medical Research Council’s (UK) criteria of a complex intervention (http://www.mrc.ac.uk/complexinterventionsguidance); the Medical Research Council’s conceptual framework guides the development and testing of the intervention. The intervention was developed to be completed in either one only session or several sessions. Some of the intervention content is more relevant to participants who have never had MDD or BD (e.g. the sections about the risk estimates of developing depression based on family history), while other sections may be more relevant to those have had an episode of MDD or BD (e.g. sections on likelihood of recurrence). However, the intervention was designed for participants to navigate website content based on their personal preference. In brief, the psycho-educational intervention includes sections on: genetic and individual and shared environmental factors; differences in genetic information and depression risk; estimating one’s risk of depression development based on family history; risk factors for recurrence of depression; role of environmental factors, including stressful life events, in determining depression risk; strategies to reduce and/or prevent depression development; childbearing decisions; suicide risk; stigma in relation to having a family history of depression; early detection, especially in children and adolescents; and early intervention. The written text of the online intervention is designed to be printable for those who would like a paper version of the tool. The sections on estimating one’s risk of depression development based on family history are presented using pictographs (also called icon arrays or “one hundred people” diagrams) to maximize comprehension [44].

### Control

Following completion of the baseline questionnaire, control group participants will be directed to a PDF of a brief generic pamphlet on depression produced by *beyondblue* (National Depression Network), 'Understanding depression’, which includes information about common symptoms of depression, criteria used to diagnose depression and treatments available. Following completion of the six-month survey, control group participants will be provided with access to intervention.

### Sample size and statistical power

The primary outcome measure will be 'intention to adopt risk-reducing strategies’; on the basis of our quantitative survey of a large nationally representative population sample of 1,046 Australian participants, we expect a mean baseline percentage of 50% of people intending to adopt a range of risk-reducing strategies [45]. Behavioral intentions were chosen as the primary outcome variable to gain an understanding of the issues related to this topic and while behavioral intentions are only an indirect measure of actual behavior, at present they are the best single predictor of future behavior in the psychological literature [46,47].

According to as yet unpublished data from the 2010 National Survey of Mental Health and Wellbeing, at least 20% of Australian residents have at least one first-degree relative with either MDD or BD. Based on similar work involving the testing of a cancer family history assessment tool, it is estimated that approximately 15% of patients will opt-in to an online trial following an invitation letter from their GP [48]. By contacting up to 500 patients for each GP practice, we expect to recruit up to 15 participants per practice.

Our sample size calculations assume an intra-class correlation coefficient (ICC) of 0.06 for patients within the same practice, consistent with ICCs observed for psychological problems in patient encounters in Australian general practice [49]. Assuming an average of twelve participants within each practice, randomizing a total of 20 GP practices will provide 80% power to detect a difference of 22% in the proportion intending to undertake risk-reducing strategies from a control proportion of 50%. This difference, corresponding to a medium effect size [50], is based on the smallest effect that would have clear public health significance and provides a sensitive indicator of clinically meaningful differences.

### Statistical methods

Analysis for the dichotomous primary outcome, intention to adopt risk-reducing strategies, will be performed using the generalized linear mixed model, which extends the standard logistic regression model to allow for clustered data. The continuous outcome of *PHQ9* will be analyzed using the linear mixed model. Adjustment for any potential confounding variables (such as age, sex, type of family history) will be made if there is important baseline imbalance in these variables between intervention groups.

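### The primary mixed model on about 20 practices names no small-sample reference, and the stated 80% power reproduces only under a normal approximation; read against z, the 5% test would run at about 6% to 7.7%

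*Protocol article*

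**What the plan says.** In the protocol article, the Design section makes the GP practice the unit of randomization. Under Statistical methods, analysis of the dichotomous primary outcome "will be performed using the generalized linear mixed model, which extends the standard logistic regression model to allow for clustered data". PHQ9 is to be analysed with a linear mixed model. Neither sentence names a test statistic, reference distribution, degrees-of-freedom method, estimation method or software.

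Under Sample size and statistical power, the calculations "assume an intra-class correlation coefficient (ICC) of 0.06 for patients within the same practice". The size statement reads "Assuming an average of twelve participants within each practice, randomizing a total of 20 GP practices", and this number of practices "will provide 80% power to detect a difference of 22% in the proportion intending to undertake risk-reducing strategies", starting from a control proportion of 50%. Allocation ratio, significance level and sidedness are not given.

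**The concern.** A random intercept per practice deals with the correlation between patients of one practice. It does not by itself deal with the fact that the between-practice variance is estimated from only 20 practices. In a two-arm comparison that leaves 20 − 2 = 18 degrees of freedom. A likelihood-fitted logistic mixed model read against z treats this variance as known. The maximum-likelihood estimate also tends to be low, so the test rejects too often and the interval is too short.

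The primary p-value and confidence interval are at stake. A result with a test statistic between 1.96 and 2.10 would be significant against z and not against t with 18 degrees of freedom. A choice that can decide the trial's conclusion should be fixed before data are seen. The PHQ9 linear mixed model raises the same question if it is read against z; no figure was computed for it.

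**Working it through.** **Inputs from Sample size and statistical power:** 20 practices, mean 12 participants per practice, ICC 0.06, 50% vs 72% (a 22-point difference), power 80%.

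**Assumptions, not stated in the article:** 1:1 allocation (10 practices and 120 participants per arm) and a two-sided 5% level.

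**1. The plan's own figure.**
- Design effect: 1 + (12 − 1) × 0.06 = 1.66.
- Effective participants per arm: 120 / 1.66 = 72.3.
- Standard error of the difference (unpooled): √[(0.50 × 0.50 + 0.72 × 0.28) / 72.3] = √(0.4516 / 72.3) = 0.0790.
- Standardised effect: 0.22 / 0.0790 = 2.783.
- Power against z: Φ(2.783 − 1.960) = 79.5%.

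This matches the stated 80%. Other normal approximations are slightly lower: 78.0% with pooled variance and 78.2% with the arcsine transformation.

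**2. The same design on 18 degrees of freedom.**
- The critical value rises from 1.960 to 2.101.
- Power from the noncentral t with noncentrality 2.783 is 74.9%.
- By the same calculation, 22 practices give 79.3% and 24 give 83.0%.

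**3. Interval width.** 1.960 / 2.101 = 0.933, so z intervals are about 7% narrower than t(18) intervals.

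**4. Simple check on the error rate.** The two-sided probability that a t variable with 18 degrees of freedom exceeds 1.96 is 6.6%.

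**5. Simulated error rate under no effect.** The set-up was 20 practices, mean 12 participants, a true proportion of 50% and ICC about 0.06. The logistic random-intercept model was fitted by maximum likelihood with 21-point quadrature. The first four rows have 8,000 trials each (Monte Carlo standard error about 0.3 points). The last two have 2,500 trials each (about 0.5 points).

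| Scenario | Wald z | Likelihood ratio | Wald statistic on t(18) | Practice-level t-test |
|---|---|---|---|---|
| Beta-binomial, equal sizes | 7.4% | 6.5% | 5.5% | 5.2% |
| Logit-normal, variance 0.21, equal sizes | 7.0% | 6.2% | 5.2% | 5.3% |
| Logit-normal, variance 0.27, equal sizes | 7.4% | 6.5% | 5.5% | 5.3% |
| Beta-binomial, varying sizes | 7.7% | 6.7% | 6.0% | 5.0% |
| Logit-normal, SD 0.52, equal sizes | 7.0% | not run | 5.0% | 4.8% |
| Logit-normal, SD 0.52, size CV 0.5 | 7.5% | not run | 5.8% | 4.6% |

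A separate simulation gave lower Wald z rates: 6.1% with equal sizes and 6.8% with size CV 0.5. The range for z is therefore about 6% to 7.7%. In runs of 3,000 trials with other ICCs and equal sizes, Wald z rejected 6.3% at ICC 0.02 and 8.1% at ICC 0.10.

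**6. Simulated power at 50% vs 72% (2,500 trials per scenario).** With equal sizes, power is 82.0% against z and 77.6% against t(18). With size CV 0.5, it is 77.5% and 72.5%.

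**The case against.** The strongest reply is that a protocol article commonly leaves the degrees-of-freedom method to the full protocol or the analysis plan, neither of which is shown. The named model respects randomization by practice, and a t reference is fully compatible with the sentence that names it. All of this stands, and the missing detail alone would be no finding.

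A reader might infer that the plan specifies a Wald test with a 7% error rate. The document does not support that: it names no test, so the inflation is conditional on how the model is read. Ten practices per arm is likewise an assumption, because only the total is given.

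The reply does not reach the power statement, which the article itself makes. The 80% is recovered with a normal approximation and not with t on 18 degrees of freedom. A planning formula does not bind the analysis, but it shows that the stated planning made no allowance for few clusters. By this calculation, 5% error and 80% power are not both available from 20 practices of 12.

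Two further limits stand. The excess is modest, and t(18) does not remove it fully when practice sizes differ. Also, the Measures section scores this outcome as a mean from 0 to 4 while Statistical methods calls it dichotomous. If the continuous score became primary, these binary simulations would not apply directly, although the limit of about 18 between-practice degrees of freedom would.

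**Conclusion.** The point holds in conditional form. If the arm effect is read against z, the nominal 5% primary test runs at about 6% to 7.7%, an excess of roughly 1 to 3 points, and its confidence interval is about 7% too narrow. Switching to the likelihood-ratio test does not cure this (6.2% to 6.7%). With a t(18) reference, the stated 80% power becomes about 75% by the analytic calculation or 78% by simulation with equal practice sizes, and about 72% with size CV 0.5.

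These figures rest on 1:1 allocation, a two-sided 5% level, ICC 0.06, all 20 practices recruited and 12 participants per practice on average. The choice of model is sound. What needs settling is the reference distribution and a power figure consistent with it.

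**What to change.** Add to Statistical methods that the arm effect and its confidence interval in the logistic mixed model are referred to t with (practices − 2) degrees of freedom, which is 18 for 20 practices. Name a t-test on practice-level proportions as a check, because t(18) still ran at about 5.5% to 6% with unequal practice sizes while the practice-level test stayed close to or below 5%. For the PHQ9 linear mixed model, specify REML with Kenward-Roger degrees of freedom.

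Restate the power under Sample size and statistical power on the same basis, giving the allocation ratio, significance level and sidedness, and showing the figures for both equal and varying practice sizes.

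In text, the cost is a sentence or two. In substance, it is a less favourable power figure, about 72% to 78% instead of 80%. If 80% is to be kept, the analytic calculation with equal sizes points to between 22 and 24 practices (79.3% and 83.0%), and unequal sizes would call for more.

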**Methods/design:**

The proposed intervention will be evaluated in the general practitioner (GPs) setting, using a cluster randomized controlled trial. GP practices will be randomized to provide either access to the online, targeted psycho-educational intervention or brief generic information about depression (control) to eligible patients. Eligibility criteria include having at least one first-degree relative with either major depressive disorder (MDD) or bipolar disorder (BD). The primary outcome measure is 'intention to adopt, or actual adoption of, risk-reducing strategies’. Secondary outcome measures include: depression symptoms, perceived stigma of depression, knowledge of risk factors for development of depression and risk-reducing strategies, and perceived risk of developing depression or having a recurrence of family history. Over the course of the study, participants will complete online questionnaires at three time points: at baseline, and two weeks and six months after receiving the intervention or control condition.

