#### Outcome measures to be administered at all time points

##### Patient health questionnaire depression (PHQ9)

The *PHQ9* is a ten-item self-administered validated instrument, which scores each of the Diagnostic and Statistical Manual of Mental Disorders (DSM-IV) criteria for MDD [37]. It can be used both as a diagnostic measure as well as a symptom severity measure and assesses depression symptoms over the past two weeks. It has 4-point Likert type response options ranging from “Not at all” to “Every day”; scores range from 0 to 27, with higher scores indicating higher levels of depression. Depression levels can be categorized as mild (5 to 9 scores), moderate (10 to 14 scores), moderately severe (15 to 19 scores) or severe depression (20 to 27).

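### Covariate adjustment waits on an undefined observed imbalance and no baseline outcome term is named, so the primary model depends on the data and available precision is forgone

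*Protocol article*

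**What the plan says.** In the protocol article, Statistical methods, the primary analysis of dichotomous intention "will be performed using the generalized linear mixed model, which extends the standard logistic regression model to allow for clustered data". For the depression score, "The continuous outcome of *PHQ9* will be analyzed using the linear mixed model". Covariates are handled in one sentence, which gives age, sex and type of family history as examples from an open list of possible confounders. The condition it attaches is that adjustment "will be made if there is important baseline imbalance in these variables between intervention groups". No level of imbalance is given at which adjustment begins, and the baseline value of the outcome is not mentioned for either model.

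That baseline value will exist. According to the abstract, "participants will complete online questionnaires at three time points: at baseline, and two weeks and six months after receiving the intervention or control condition". The Measures section lists PHQ9 and the intention/adoption scale under the heading "Outcome measures to be administered at all time points". Baseline also comes before exposure: "Following completion of the baseline questionnaire, intervention group participants will be directed to the intervention", and the Control section gives the same order for the pamphlet.

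**The concern.** Two things follow from this rule.

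First, the choice between an adjusted and an unadjusted primary analysis is made after looking at the data, against an undefined standard and from an open list of covariates. Two analysts who both follow the text could report different primary estimates. In a logistic mixed model this affects more than precision. Adding a prognostic covariate changes the conditional odds ratio being estimated, so the target quantity itself stays open until the data are in.

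Second, a covariate that relates to outcome improves precision whether or not the arms happen to differ on it. A rule that waits for imbalance gives up most of that benefit. The trial randomizes only 20 practices. Under Study procedures, GPs screen patients, and the invitation letter then directs each patient to the website of the practice's arm. Baseline differences could therefore arise from chance or from recruitment, and either is a reason to fix the prognostic covariates in advance.

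**Working it through.** **Inputs.** From Sample size and statistical power: 20 practices, an average of 12 participants each (240 in total), control proportion 50%, difference 22 points, power 80%, and the calculations "assume an intra-class correlation coefficient (ICC) of 0.06 for patients within the same practice". Assumed because the article does not state them: two-sided alpha 0.05, 1:1 allocation (120 per arm), and the baseline to follow-up correlation r, shown as a range.

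**1. The plan's own figure.**
- Design effect = 1 + (12 − 1) × 0.06 = 1.66. Effective n per arm = 120 / 1.66 = 72.3.
- SE = √[(0.50 × 0.50 + 0.72 × 0.28) / 72.3] = √(0.4516 / 72.3) = 0.0790.
- 0.22 / 0.0790 = 2.78, and Φ(2.78 − 1.96) gives 79.5% power.

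The stated 80% reproduces with no covariate adjustment. With pooled variance the figure is 78.0%.

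**2. Continuous outcome (PHQ9).** Under linear adjustment the residual variance is multiplied by 1 − r², and the equivalent sample is multiplied by 1 / (1 − r²).

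| r (assumed) | Variance falls by | Equivalent extra patients |
|---|---|---|
| 0.5 | 25% | 1/0.75 = 1.33, so 33% |
| 0.6 | 36% | 1/0.64 = 1.56, so 56% |
| 0.7 | 49% | 1/0.51 = 1.96, so 96% |

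**3. Dichotomous primary outcome.** Suppose r describes an underlying normal score and the outcome is that score split at its median (an assumption, consistent with a 50% control proportion). Two versions of the baseline covariate are possible:
- Baseline also split: correlation = (2/π) arcsin r.
- Baseline kept as a score: correlation = r √(2/π) = 0.798 r.

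| r | Split baseline: correlation, variance fall | Score baseline: correlation, variance fall |
|---|---|---|
| 0.5 | 0.33, 11% | 0.40, 16% |
| 0.6 | 0.41, 17% | 0.48, 23% |
| 0.7 | 0.49, 24% | 0.56, 31% |

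The equivalent sample gain runs from 1/0.89 = 1.13 (13%) to 1/0.69 = 1.45 (45%).

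In power terms, against the 78.0% pooled reference, multiplying variance by 0.91, 0.75 or 0.64 gives 81.8%, 88.5% or 92.9%. The range above (0.89 to 0.69) lies inside those points. These are linear approximations. In the logistic model the gain shows up in the test and in a marginal risk difference, not as a smaller standard error of the log odds ratio.

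**4. What the trigger does.** Take an assumed trigger of 0.2 SD on one covariate with the same ICC. The arm difference has SD √(2 × 1.66 / 120) = 0.166, so chance alone exceeds the trigger with probability 2 × [1 − Φ(0.2 / 0.166)], about 23%.

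A simulation of 20 practice means covered a continuous outcome, ICC 0.06, and an effect of 2.8 × 0.166 = 0.47 SD, with 10,000 trials per setting. The baseline outcome was the covariate.

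| r | Power: never / triggered / always | Type I error: never / triggered / always |
|---|---|---|
| 0.3 | 76.3 / 76.2 / 77.6% | 4.6 / 4.2 / 4.7% |
| 0.5 | 75.0 / 77.3 / 83.9% | 5.1 / 3.8 / 4.8% |
| 0.7 | 76.1 / 82.3 / 95.0% | 4.7 / 2.7 / 4.9% |

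The triggered rule recovers (77.3 − 75.0) / (83.9 − 75.0) = 26% of the gain at r = 0.5 and (82.3 − 76.1) / (95.0 − 76.1) = 33% at r = 0.7. It recovers none at r = 0.3.

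**The case against.** The best defence is that the article is condensed. It lists no fixed effects, time terms or random-effect structure, and silence on the baseline outcome is not exclusion. A linear mixed model over three time points might carry baseline PHQ9 as a repeated response, and a fuller plan may name it. This stands in part: the article does not show that baseline is excluded, only that it is not named. It does not rescue the trigger, which is a stated rule. If the open list is read to include the baseline outcome, that value enters only once imbalance has been seen.

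A second defence is that the gain for PHQ9 should not be carried over to the primary outcome. That is right, and the two are kept apart above. If r is small, the gain is small for either.

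A reader might also argue that the top stage of the scale, behaviour kept up for more than six months, must pre-date the intervention at the two-week assessment, so that baseline is built into the primary outcome. That holds for the 0 to 4 score under Measures. The model in Statistical methods is for dichotomous intention, and the article does not say how that stage is classified there, so the argument cannot be used for the primary model.

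**Conclusion.** The point holds as a fault in a stated rule. The adjustment trigger is undefined and depends on the data, it leaves the conditional odds ratio of the primary model unsettled, and it forgoes precision from baseline values the trial already collects. The size rests on an assumed r of 0.5 to 0.7: 33% to 96% more patients in effect for a continuous outcome, and about 13% to 45% for the primary outcome under the median-split assumption.

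Two stronger readings are not supported. One is that the trial is underpowered against its own claim. The stated power reproduces at 79.5% without adjustment, so what is given up is additional efficiency. The other is that choosing the model after seeing imbalance inflates false positives. In the simulation the rule was conservative, with type I error of 2.7% to 4.2%. That result covers one fixed threshold on one covariate, and not the discretion that an undefined threshold allows.

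Nothing here invalidates the trial. The change should be made because it costs no data.

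**What to change.** Replace the adjustment sentence in Statistical methods with:

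> All models adjust for the baseline value of the outcome (for the primary outcome, the baseline intention/adoption score) and for a short fixed list of age, sex, type of family history and personal history of MDD/BD, whatever the observed balance; the unadjusted analysis is a sensitivity analysis.

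For the logistic primary model, report a marginal risk difference alongside the odds ratio. The sample size was set on a difference in proportions, and a marginal difference keeps the same meaning whichever covariates are in the model.

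The cost is wording only. Age and sex are in the baseline socio-demographic data, the Family History Screen supplies family and personal history, and the outcome scales are already completed at baseline. The change should be made before any outcome data are compared by arm.
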